### Baseline Site Assessments

3.4

The baseline efficiency of each hospital's colonoscopy surveillance process will be determined by calculating the staffing time burdens and costs for surveillance colonoscopy, as well as the appropriateness of each given surveillance interval, and time taken from colonoscopy until the patient receives communication regarding their next interval recommendation.

As per usual hospital practice, the next recommended colonoscopy surveillance interval will be provided to the patient and their family physician by the clinical team after colonoscopy. Compliance rates will be compared to the Australian guidelines for surveillance colonoscopy [6], and the time for each patient and their family physician to receive communication regarding the surveillance interval will be determined from medical records in a random selection of 10% of the total colonoscopies completed in 1 year (5% performed for surveillance and 5% for non‐surveillance indications) per hospital. Staffing time to provide the recommendations and communications will be prospectively determined for a minimum of 50 individuals undergoing surveillance colonoscopies at each hospital, with the costs calculated through consideration of time and salary rates. Clinical teams that are involved with the surveillance processes (proceduralists, nurses, administration and family physicians) will be interviewed to collect qualitative data on acceptability and limitations of current practices.

Surveys will be collected from a random selection of 100 patients per hospital before and after their surveillance colonoscopy, capturing patient demographics, assessing colonoscopy experience, quality of life and the quality of endoscopic services provided. Quality of life will be determined using the EQ‐5D‐5L validated measure [36].

Key performance indicators for the quality of endoscopic services (using recommendations provided in several consensus reports [6, 37, 38]; Table S1) will be calculated for a period of at least 6 months.

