**FIGURE 1 cam471456-fig-0001:**
[figure not shown]
A digital healthcare approach for automated colonoscopy surveillance recommendations, integrated with a nurse‐coordinated program.

Patients and family physicians will be informed of the prescribed surveillance interval and when the next surveillance colonoscopy is due, with the timing from colonoscopy until this communication recorded. Online surveys capturing the same patient‐reported measures collected at baseline will also be offered before and after surveillance colonoscopy, commencing at each hospital, 6 months after implementation of the intervention. In addition, interviews will be conducted with the clinical teams involved in the surveillance processes (proceduralists, nurses, administration and family physicians), to gauge end‐user acceptability. Measures of the key performance indicators for the quality of endoscopic services (Table S1) will be repeated at least 6 months after implementation of the intervention at each site.

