### Outcome Parameters

3.10

All study outcomes will be compared between baseline and post‐intervention measures. The primary outcome is the proportion of automated interval recommendations for surveillance colonoscopy that match those derived from a prespecified ruleset directly based on the Australian guidelines. This ruleset serves as the gold standard for interval assignment and is explicitly programmed from the most recent national surveillance criteria. Algorithm outputs will be independently compared against this reference ruleset, with nurse recommendations serving as a secondary comparator. Validation will be conducted blinded to algorithm outputs to avoid bias, and any discrepancies between algorithm, ruleset and clinical recommendations will be adjudicated by an independent gastroenterologist panel.

Secondary outcomes include:
The timing of the scheduled colonoscopy in relation to the recommended timeframe, with ‘on‐time’ colonoscopy defined as occurring within ±6 months of the due date specified by guideline recommendations.The time taken to review the colonoscopy outcomes and communicate the prescribed surveillance interval with the patient and family physician.The prevalence of individuals lost to follow‐up.The prevalence of patients with acceptable bowel preparation quality, complete intubation and adequate withdrawal time.The incidence rate for advanced neoplasia (with hierarchical classification prioritising invasive CRC > stage 0 CRC > advanced adenoma), including CRC, adenomatous polyps or sessile serrated lesions ≥10 mm in size, with villous change, or with high‐grade dysplasia, sessile serrated lesions with any dysplasia and any traditional serrated adenoma.The incidence rate for adverse events (e.g., bleeding, perforation, hospitalisation and death).Acceptability of the intervention to patients and clinical teams.Cost‐effectiveness of the intervention.Among the secondary outcomes, those relating to colonoscopy quality metrics and timeliness are confirmatory and prespecified, whereas patient‐reported measures and thematic feedback analyses are exploratory.

Trial findings will be reported according to the CONSORT‐AI extension guidelines [42].

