Where relevant, univariate followed by multivariable modelling will be undertaken by adding variables considered clinically important or statistically significant from the univariate model to adjust for confounding effects. Hospitals will be treated as random effects, and main effects will be the intervention group; that is, before and after implementation of the intervention. Missing data will be handled using multiple imputation under the missing‐at‐random assumption. For bowel preparation quality, missing values will be imputed as ‘adequate’ in the primary analysis, reflecting routine clinical documentation where poor preparation is explicitly noted, with sensitivity analyses applying conservative rules assumption imputing missing values as ‘poor’.

Multivariable generalised linear models and pairwise comparisons will be used to assess the association between patient‐reported measures (such as satisfaction with the colonoscopy experience) and acceptance of the digital healthcare approach. Thematic analysis will be conducted to establish clinical end‐user opinions on the surveillance program. Prespecified subgroup analyses will assess intervention effects across patient age, sex, socioeconomic status (by postcode linkage) and hospital location, with multiplicity controlled via Holm–Bonferroni correction. To ensure equitable healthcare delivery, analyses will include age groups ≥ 75 years, comorbidity burden (based on the Charlson Comorbidity Index categories), socioeconomic status and regional vs. metropolitan location.

Quality of life measures will be used to calculate the incremental costs before and after implementation of the intervention per quality‐adjusted life‐year gained (QALY) in a model‐based economic evaluation. Implementation costs will be obtained from administrative data. The economic evaluation will adopt a health‐system perspective with a 12‐month time horizon, 5% annual discounting and QALY derivation from EQ‐5D‐5L value sets. Probabilistic sensitivity analyses will assess parameter uncertainty, and reporting will align with CHEERS 2022 guidelines [43]. Patients will be recruited consecutively at each site, with reminders and follow‐up strategies implemented to maximise retention. Missing responses in surveys and quality‐of‐life instruments will be addressed using multiple imputation under the missing‐at‐random assumption, consistent with the approach for clinical outcomes.

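### Communication time has no stated rule for episodes where the interval was never communicated; the blanket imputation rule would give them an ordinary finite time

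*Protocol article*

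**What the plan says.** All references are to the protocol article.

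- **Outcome (section 3.10).** The secondary outcomes include "The time taken to review the colonoscopy outcomes and communicate the prescribed surveillance interval with the patient and family physician". The same section classes timeliness outcomes as confirmatory, while patient-reported measures and thematic feedback are exploratory.
- **Usual-practice data (section 3.4).** At baseline, "the time for each patient and their family physician to receive communication regarding the surveillance interval will be determined from medical records", in a random 10% sample of one year's colonoscopies per hospital. The section describes usual practice as one in which "the next recommended colonoscopy surveillance interval will be provided to the patient and their family physician by the clinical team after colonoscopy".
- **Intervention data (section 3.8, text after Figure 1).** Patients and family physicians are told the interval, "with the timing from colonoscopy until this communication recorded".
- **Test (section 3.12).** Continuous measures are assigned Wilcoxon and Kruskal–Wallis tests. No censoring, time-to-event or worst-rank method is named.
- **Missing data (section 3.12).** "Missing data will be handled using multiple imputation under the missing‐at‐random assumption". One clinical variable has its own rule: "For bowel preparation quality, missing values will be imputed as ‘adequate’ in the primary analysis", with a sensitivity analysis that imputes the opposite value.

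**The concern.** Both measurement descriptions presuppose that a communication took place. Where none did, the episode has no time. The value is not an unknown finite number; it is absent because the event did not occur, which is the worst result this outcome can take. Missing at random is then implausible, because absence is itself the outcome. An imputation model fitted to communicated episodes can return only finite times, so a complete failure is scored as an ordinary delay. Dropping the episode hides it just as well.

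Section 1 says that multi-step referral between specialists and family physicians puts patients at risk of being lost. If such failures are commoner under usual practice than under SCOPES, the stated rule removes that part of the difference from an outcome the article calls confirmatory. The primary outcome, guideline concordance, is not affected.

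**Working it through.** **No figure to reproduce.** The article gives no power statement, expected difference or non-communication rate for communication time. Its 60% to 75% power statement concerns guideline concordance. Everything numerical below is an assumed illustration.

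**Step 1: which stated rule reaches such an episode.** The outcome is a time and so falls under the rank tests. With no communication there is no time to rank. The only stated rule for an absent value is imputation under missing at random, and the only clinical variable exempted is bowel preparation. The text therefore leads to imputation or, failing that, omission.

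**Step 2: simple arithmetic (assumed inputs).** Let 90% of informed patients be informed within 8 weeks in both phases. Let the never-informed share be 10% to 30% in usual practice and 2% under SCOPES.

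- Imputed from the informed, or dropped: 90% versus 90%, difference 0.
- All episodes counted, usual practice: 0.90 × (1 − 0.10) = 0.81, down to 0.90 × (1 − 0.30) = 0.63.
- All episodes counted, SCOPES: 0.90 × 0.98 = 0.882.
- Difference: 0.882 − 0.81 = 0.07 to 0.882 − 0.63 = 0.25.

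**Step 3: simulation (assumed inputs).** There were 400,000 episodes per phase. Informed times were lognormal with sigma 0.8 and median 30 days in both phases, with 2% never informed under SCOPES. Imputation drew from the informed episodes without covariates. It gave medians of about 30 days in both phases, a probability of about 0.50 that a SCOPES episode is faster, and about 91.5% informed by day 90 in both phases, at every rate tried. Ranking the never-informed as worst gave:

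| Never informed, usual practice | Median days, usual practice vs SCOPES | P(SCOPES faster) | Informed by day 90, usual practice vs SCOPES |
|---|---|---|---|
| 2% | 30.6 vs 30.7 | 0.499 | 89.8% vs 89.6% |
| 5% | 31.7 vs 30.6 | 0.516 | 86.9% vs 89.7% |
| 10% | 33.5 vs 30.7 | 0.540 | 82.3% vs 89.7% |
| 20% | 38.7 vs 30.6 | 0.590 | 73.2% vs 89.6% |
| 30% | 47.0 vs 30.6 | 0.640 | 64.2% vs 89.7% |

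With equal non-communication (first row) the contrast is unchanged.

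**Step 4: when informed patients also hear sooner.** With medians of 30 versus 14 days and 20% versus 2% never informed, imputation shows 91.5% versus 99.0% by day 90 (7.5 points). Worst rank shows 73.3% versus 97.1% (23.8 points). The difference is reduced but not erased, so the zero in steps 2 and 3 comes from assuming equal times among the informed.

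**Step 5: the opposite error.** Take the 20% row and suppose that every absent record, in both phases, was really a communication nobody documented, with the same distribution of times. The truth is then about 91.5% in both phases, and counting absent records as failures creates a false difference of 89.6 − 73.2 = 16.4 points in favour of SCOPES. The same data support either reading, so both need to be reported.

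**The case against.** The strongest reply is that no section says an uncommunicated episode is coded as missing. If non-communication is an event that did not happen, it is arguably not missing data, and the imputation rule does not reach it. A worst rank would fit the named tests without changing a word, and an unseen analysis plan may already say so. This stands to the extent that a reader should not infer that the article expressly orders imputation of these episodes. It does not dispose of the point. The article fixes a general rule and one exception, and that exception shows the authors recognise that an absent record can carry meaning. An analysis plan that followed section 3.12 would inherit the gap.

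A second reply is that frequent non-communication is not shown. Section 3.4 describes usual practice as providing the interval, and section 1 speaks of many systems, not of these hospitals. This stands: the rate is unknown.

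A third reply is that loss to follow-up and on-time colonoscopy, both separate secondary outcomes, may pick up these patients. This is partial cover only. Neither is linked to communication in the text, and neither captures a family physician who was never told.

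The most important reply is that an absent record is not proof of no communication. Baseline times come from charts and SCOPES times from programme recording, so documentation gaps may well be commoner at baseline. This stands and shapes the fix: scoring every unrecorded episode as a failure, with no check, could bias the result towards SCOPES.

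**Conclusion.** The point holds in a limited form. For a confirmatory timeliness outcome, the only rules stated would turn non-communication into an ordinary delay or remove it. If non-communication is commoner in usual practice, the contrast is biased towards no difference; if rates are equal, little changes.

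The size cannot be obtained from the article. A reader might infer that a true difference of 7 to 25 points will be reported as zero. The documents do not support that, because those figures rest on assumed rates and on equal times among informed patients. Nor do they support treating every episode without a record as a failure. The conclusion rests on reading the general imputation rule as covering absent communication times, which is the reading the text leaves but not one it spells out.

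**What to change.** 1. Exempt communication time from the blanket imputation rule.
2. Analyse time from colonoscopy to documented communication as time to event, censored at one common horizon in both phases. Alternatively, give episodes without communication the worst rank.
3. Report the proportion with documented communication by a fixed day over all audited episodes, for patient and family physician separately, in the period-adjusted mixed model.
4. Where possible, ascertain communication from the same type of record in both phases.
5. Add a sensitivity analysis that treats absent records as undocumented communication with imputed times, parallel to the two-way rule already stated for bowel preparation.

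The cost is mainly wording and a little more analysis on the same audited records; item 4 may need some alignment of record sources. The downside is that the main estimate may count some documentation gaps as non-communication, which item 5 is there to expose.

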### Sample Size and Power

3.11

The stepped‐wedge cluster randomised trial includes five local health networks (cluster) with eight participating hospitals, contributing an average of 1417 colonoscopy episodes per 3‐month period (adjusted for 10% attrition) across seven sequential periods (one baseline and six rollout steps). Assuming an ICC of 0.01, a baseline guideline concordance of 60%, and an expected post‐implementation improvement to 75% (15% absolute increase), the design archives approximately 90% power at a two‐sided *α* = 0.05 under a binomial mixed‐effects model. Power was estimated via simulation (*n* = 1000 iterations per effect size), incorporating cluster and period fixed effects. A power curve (Figure S1) illustrates sensitivity to effect size assumptions, a stepped‐wedge design diagram (Figure S2) depicts the rollout sequence, and a summary of power estimates across effect sizes is presented in Table S3.

For the patient‐reported outcomes, assuming eight hospitals with paired before and after implementation (100 participants per hospital per period, total *N* = 1600), we estimate > 80% power (*α* = 0.05, two‐sided) to detect a small‐to‐moderate standardised mean difference (Cohen's *d* ≈ 0.25–0.30) in EQ‐5D‐5L scores, accounting for within‐cluster correlation (ICC ≤ 0.02) and within‐period correlation of repeated measures (*ρ* ≈ 0.5). This is appropriate for evaluating meaningful changes in patient‐reported measures at the hospital level.

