### Implementation of the Digital Process

3.8

This trial will compare a control phase (usual practice) with an intervention phase (the nurse‐coordinated program integrated with digital processes [i.e., SCOPES]) using a stepped‐wedge cluster trial design [40]. Implementation will commence in the second year of the study, where one new hospital network will have the intervention implemented every 6 months, until all five included South Australian hospital networks receive the intervention. The stepped‐wedge design can provide greater statistical power than a randomised parallel group cluster trial design under certain conditions, such as moderate intra‐cluster correlation (ICC), adequate cluster size and multiple steps, with fewer time constraints in the introduction of the digital processes [41]. Each hospital network is expected to perform up to 10,000 colonoscopies per year and will receive the intervention phase for at least 12 months.

Figure 1 provides an overview of the digital processes. Following the automatic upload of colonoscopy and associated pathology data into the clinical registry, the SCOPES algorithm will provide a surveillance recommendation. Each recommendation will be reviewed and approved by a trained nurse. In cases where the nurse and algorithm identify discrepant surveillance interval recommendations, conflicts will be resolved by a third‐party nurse or proceduralist as appropriate. All reasons for discrepant surveillance intervals will be recorded for quality improvement purposes.

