### Statistical Analyses

3.12

All sites will be allowed a three‐month post‐implementation period of transition before outcome measurement. Temporal confounding will be mitigated through the use of models (e.g., interrupted time series analysis) which adjust for secular trends. Given the stepped‐wedge cluster randomised design, analyses will explicitly include fixed effects for time period and intervention status, and random effects for site (cluster) to account for ICC. With only eight clusters, we will apply the Kenward–Roger correction to adjust standard errors and *p* values are not inflated due to small number of clusters. Data analysis will be conducted using Python (3.11) and R (version 4.4.1).

The percentage of surveillance recommendations that match with Australian guidelines will be calculated from audit data, and the prevalence of individuals lost to follow‐up, prevalence of those with acceptable colonoscopy quality, and incidence rates for advanced neoplasia and adverse events will be summarised using descriptive statistics. All measures will be directly compared to each site's own baseline measures in a paired manner using McNemar's tests for proportions, Wilcoxon and Kruskal–Wallis signed‐rank tests for continuous measures and mixed‐effects Poisson regression for incidence rates. Analyses will be conducted on an intention‐to‐treat basis. A prespecified generalised linear mixed model (GLMM) with a logit link will be used for the primary binary outcome (guideline concordance) including fixed effects for time period and intervention, random intercepts for clusters and adjustment for potential confounders (e.g., age, indication and baseline quality metrics). To address the small number of clusters (*K* = 5), we specify that inference will be based on cluster‐preserving parametric bootstrap for both the intervention coefficient and marginal contrasts. Multiple comparisons across secondary outcomes will be controlled using Holm–Bonferroni correction to limit type I error. Additional sensitivity analyses will include (i) cluster‐level summaries with Kenward–Roger correction, (ii) generalised estimating equations with small‐sample corrected SEs and (iii) permutation tests at the cluster level. If national guideline text changes during the trial, an indicator for the new guideline will be included, and analyses will be repeated using both old and new mapping.

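### The 90% power statement describes six rollout steps in 3-month periods, which section 3.8 does not have, and its own inputs give power above 99.9%

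*Protocol article*

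**What the plan says.** Section 3.11 (Sample Size and Power) gives five networks as clusters, containing eight hospitals, and an average of 1417 episodes per 3-month period after 10% attrition, "across seven sequential periods (one baseline and six rollout steps". With ICC 0.01, concordance rising from 60% to 75% and two-sided alpha 0.05, it states that "the design archives approximately 90% power". The simulation is described as "incorporating cluster and period fixed effects". The text does not say whether 1417 is per network, per hospital or for all sites together.

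Section 3.8 (Implementation of the Digital Process) starts rollout in year 2. From then "one new hospital network will have the intervention implemented every 6 months", until all five have it, and each network "will receive the intervention phase for at least 12 months".

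Section 3.12 (Statistical Analyses) allows every site a 3-month transition before outcomes are measured. It specifies "random effects for site (cluster) to account for ICC" and, for K = 5, inference by a cluster-preserving parametric bootstrap. It takes the matching percentage from audit data. The only audit fraction given is the baseline one in section 3.4: a "random selection of 10% of the total colonoscopies completed in 1 year" per hospital, half of it surveillance.

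**The concern.** This is the only power justification given for the primary outcome, and two things in it look wrong on their face.

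First, five networks crossing singly make five steps, not six, and the steps are 6 months apart, not 3. The powered layout and the planned rollout cannot be the same design.

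Second, a 15-point difference with over a thousand episodes per period and ICC 0.01 should give power far above 90%, so an input or a label is probably wrong.

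At stake is whether anyone can tell what the trial can detect. A power figure that comes from neither the stated inputs nor the planned schedule gives no guidance on the detectable difference or on how many episodes need assessing per network and period.

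**Working it through.** **Schedule.** Section 3.11: 7 × 3 = 21 months. Section 3.8: five crossovers 6 months apart span 4 × 6 = 24 months, and the last network's 12 months makes at least 36 months from first crossover. With a 3-month baseline and 6-month spacing, crossovers fall at months 3, 9, 15 and 21, so only three networks would be treated inside the 21-month window. The 3-month transition is one whole period of the powered layout.

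**Reproducing the stated 90%.** Inputs from section 3.11: I = 5 clusters, T = 7 periods, ICC 0.01, difference 0.15, two-sided 0.05. My choices: crossovers at periods 2 to 6, risk-difference scale, total variance at the mean rate 0.675.

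- Total variance = 0.675 × 0.325 = 0.2194. Between-cluster variance τ² = 0.01 × 0.2194 = 0.002194. Cell-mean error variance σ² = 0.99 × 0.2194 / m, for m episodes per network-period.
- Hussey–Hughes: Var = I σ²(σ² + Tτ²) / [(IU − W)σ² + (U² + ITU − TW − IV)τ²].
- Treated cells: U = 6+5+4+3+2 = 20. Squared period totals: W = 0+1+4+9+16+25+25 = 80. Squared cluster totals: V = 36+25+16+9+4 = 90. So IU − W = 20 and U² + ITU − TW − IV = 400 + 700 − 560 − 450 = 90.
- m = 1417: σ² = 0.0001533; Var = 5 × 0.0001533 × 0.01551 / (0.003065 + 0.19744) = 0.0000593; SE = 0.0077; z = 19.5.
- m = 1417/5 = 283: SE = 0.0170; z = 8.8.
- Power = Φ(0.15/SE − 1.96). Detectable difference at 90% power = 3.242 × SE.

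The documents give no cluster autocorrelation (CAC), so I varied it from 1 to 0:

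| Reading of 1417 | m per cell | SE, CAC 1 to 0 | Power | Detectable at 90% |
|---|---|---|---|---|
| Per network | 1417 | 0.0077 to 0.0242 | >99.9% | 2.5 to 7.9 points |
| All networks, per period | 283 | 0.0170 to 0.0272 | >99.9% | 5.5 to 8.8 points |
| Whole trial (1417/35) | 40.5 | 0.0427 to 0.0448 | 92 to 94% | 13.8 to 14.5 points |

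(In the last row the extreme is at CAC 0.5.) Reading 1417 as per hospital gives still larger cells (1417 × 8/5 = 2267 per network). Binomial simulations of 1000 runs with cluster and period fixed effects gave power 1.000 at both 1417 and 283 per cell.

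About 34 episodes per cell suffice for 90% at CAC 1 (38 at CAC 0.5). With fixed cluster effects, the whole-trial reading gives 90.7% by formula and 89.8% by simulation. That matches the stated figure but contradicts the words about a 3-month period.

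**The section 3.8 schedule.** Assumptions: 12-month baseline (inferred from a year-2 start), quarterly cells, crossovers at quarters 5, 7, 9, 11 and 13, first quarter after each crossover dropped, 12 months after the last crossover (16 quarters). Normal approximation, CAC 1 to 0:

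| m per network-quarter | Power |
|---|---|
| 1417 or 283 | >99.9% |
| 71 (5% of 1417) | 99.9% |
| 28 (10% of 283) | 95 to 97% |
| 14 (5% of 283) | 78 to 82% |

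The percentages in the first column apply the baseline audit fraction to every cell, which is an assumption. On a t with 3 df, also an assumption and a severe one, the 28 row falls to 68–73% and the 14 row to 47–51%.

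**The case against.** The strongest defence is that seven periods may mean baseline, five steps and a final all-treated period, with the detail in supplementary material not shown. That could explain the count of seven. It does not fit the words about six rollout steps, and it leaves 3 months against 6.

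A second defence is that every reading of 1417 as a per-period number gives more power than claimed, so the error is on the safe side. This stands, and it limits the point.

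A reader might go further and infer that the trial is underpowered, with power perhaps as low as 53%. The documents do not support that. Such a figure needs the seven-period layout that section 3.8 contradicts, a t with 3 df in place of the planned bootstrap, and the 10% baseline audit fraction in every cell. Section 3.1 says audits will be repeated but gives no later fraction. Section 3.2 includes all colonoscopies, and under section 3.8 the algorithm's recommendations are each reviewed by a nurse. Nor is the non-surveillance half of the audit necessarily lost, since section 3.4 assesses interval compliance in both halves.

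Two further mismatches carry little weight. Section 3.11 names a mixed-effects model as well as cluster fixed effects, so the phrase may be loose; at CAC 1 the two give nearly the same SE (0.0173 fixed against 0.0170 random at 283 per cell). Dropping the transition quarter from the stated layout still leaves 99.2% or more at 283 or 1417 per cell.

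**Conclusion.** Wrong as written. The step count and period length in section 3.11 contradict section 3.8, and the transition in section 3.12 is not mentioned. The stated inputs give power above 99.9%, not about 90%. The difference detectable with 90% power is about 2.5 to 8.8 points, depending on what 1417 means and on the assumed CAC. The near-match when 1417 is a whole-trial total points to a labelling or input error, but only the simulation code can confirm that.

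The direction matters: this is not evidence of too small a trial. On the section 3.8 schedule, under the assumptions listed, power falls below 90% only with something added that the documents do not state, such as about 14 assessed episodes per network-quarter, or the 3-df t with small audit cells.

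**What to change.** 1. State whether 1417 is per network, per hospital, per period overall or for the whole trial, and check it against the simulation code and Table S3.
2. Reconcile the number of steps and the period length in section 3.11 with section 3.8.
3. Rerun the simulation with five crossovers 6 months apart, transition cells removed, the number of episodes that will actually be assessed per network-period, the random-intercept model and the planned K = 5 bootstrap.
4. Replace the 90% with the resulting power and detectable difference over a range of ICC and CAC. Label any audit-fraction or small-df scenario as an assumption.

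Cost: a few hours of simulation and replacement text. No extra patients are needed.
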